**Methods/Design:**

This is a single-center, prospective, randomized, controlled trial. One hundred and twenty patients with spinal bone metastases will receive palliative radiation therapy at the Heidelberg University Hospital. SBRT will be given in five or ten fractions with or without SIB. Four treatment arms are planned: IMRT with 30 Gy in ten fractions, IMRT with 30 Gy in ten fractions and SIB to 40 Gy, IMRT with 20 Gy in five fractions, and IMRT with 20 Gy in five fractions and SIB to 30Gy in five fractions will be compared. The target parameters will be measured at baseline level and at three and six months after radiation.

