This study aims at evaluating therapeutic outcomes in terms of local control through a higher biological dose in the tumor area by using SIB-IMRT and to test shortened fractionation schedules in palliative patients. Toxicity, fatigue, and QoL improvements will be evaluated. To the best of our knowledge, no comparable randomized study has been described in the literature so far.

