## Methods/Design

This is a prospective, randomized, single-center, controlled, exploratory intervention study with four parallel treatment groups aimed at comparing local control rates after RT with and without SIB in patients with bone metastases of the spine. Four different schedules will be evaluated: IMRT with 30 Gy in ten fractions to the whole vertebral body, IMRT with 30 Gy in ten fractions to the whole vertebral body with the application of a SIB to 40 Gy, 20 Gy in five fractions to the whole vertebral body or IMRT with 20 Gy in five fractions to the whole vertebral body with the application of a SIB to 30 Gy. Before enrolment in the study, patients will receive CT and if necessary magnetic resonance imaging (MRI)-based staging examinations to measure the spinal cord dimension. If intraspinal metastases are suspected, an MRI examination is performed beforehand.

RT is performed in systemic/targeted therapy free interval. Radiation therapy will be applied in five fractions per week (Monday to Friday).

After recording the baseline measurements, patients will be randomly assigned to one of the four groups. Target parameters will be measured and recorded at baseline (t_1_), at week 12 (t_2_), and again at week 24 (t_3_) (Fig. 1). Follow-up measurements are scheduled to take place at 12, 18, and 24 months after the completion of RT (Fig. 2).

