### Recruitment and randomization

The patients will be given all the relevant information about the study by the radiation oncologist at their first presentation to our department (approximately 1–2 weeks before the start of RT). If patients are interested in participating in the study, they will receive a second appointment in order to further inform them and to obtain informed consent. A block randomization procedure will be used to ensure even distribution of patients into the four groups. The randomization procedure will be carried out by a central office. The study personnel responsible for the recruitment and patient care will have no access to the randomization information and the study director will have no influence on the recruitment of patients. The recruitment phase will be concluded with the attainment of the planned number of patients (120 patients in total, 30 patients in each group). Projected recruitment time will be 12 months, and recruitment is scheduled to start in February 2017. Regular study follow-up will end two years after enrolment or, where applicable, with the respective patient’s death.

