### Statistical analysis

Due to the explorative character of this study, it was not possible to estimate the total number of cases; with a scheduled number of 30 patients per group, it will, however, be possible to detect a standardized mean-value effect (Cohen’s d) of 0.74 with a power of 80% and a significance level of 5%, if a one-factorial variance analysis is calculated. All variables will be analyzed descriptively by tabulation of the measures of the empirical distributions. In case of continuous variables mean values, standard deviations, median, minimum, and maximum values will be documented. Categorical variables will be documented as occurrence and percentage. The primary endpoint will be measured by CT. Results will be presented at three months after completion of RT and differences between groups will be calculated using a one-factorial variance analysis. Differences of categorical variables will be calculated with the Chi-square test. The survival analysis will be performed using the Kaplan–Meier method and log-rank test.

All statistical analyses will be carried out descriptively using SAS software Version 9.4 or higher (SAS Institute, Cary, NC, USA).

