## Discussion

Palliative therapy aims to relieve suffering during all stages of disease and does not have to be limited to end-of-life care. Despite advances in palliative therapies, cancer is still a great burden for patients and painful vertebral bone metastases can strongly reduce the patients’ wellbeing. Limitations of QoL, such as posture changes, reduced movement and pain, fractures, and immobility, can be consequences of vertebral metastases. Therefore, improved QoL in this palliative situation is of pivotal importance. RT has been established as an effective local treatment for vertebral metastases. Therapy goals are a reduction in pain and fatigue, improvement of QoL, prevention of pathological fractures, or neurological deficits.

For patients with vertebral metastases, dose escalations may result in improved tumor control. Since the standardized irradiation volume comprises the spinal cord, it is not possible to reduce radiation doses to the spinal cord even with modern technologies such as IMRT. Adding a SIB to the treatment may result in significant dose reductions in the spinal cord compared to conventional IMRT. Recent trials tested 30 Gy in ten fractions and 40 Gy in five fractions to bone metastases respectively, but these doses are most likely insufficient regarding local tumor control. Therefore, our hypothesis holds that a SIB to the bone metastasis might overcome this problem. A previously published planning study by Lee et al. has shown that IMRT can deliver the concomitant hypofractionated regime proposed and offer benefits in dose delivery. IMRT and VMAT are currently preferred for their superior pre-treatment verification results and shorter planning times [19]. Potential influence on the local control rate of the different IMRT techniques will be investigated in this study. Specifically, the differences in conformity and homogeneity of helical IMRT vs step-and- shoot or VMAT-IMRT techniques are examined in a subgroup analysis.

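### The four arms cross SIB with schedule, but the planned one-factorial ANOVA attributes a difference to neither and leaves the 60-versus-60 comparisons unused

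*Protocol article*

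**What the plan says.** The abstract describes the design as two crossed choices: "SBRT will be given in five or ten fractions with or without SIB". The Radiotherapy section gives the cells: 30 Gy in ten fractions, the same with SIB to 40 Gy, 20 Gy in five fractions, and the same with SIB to 30 Gy. Recruitment and randomization fixes "120 patients in total, 30 patients in each group".

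Two aims are stated. Methods/Design says the study is "aimed at comparing local control rates after RT with and without SIB in patients with bone metastases of the spine", and the Discussion frames the hypothesis in the same terms: "our hypothesis holds that a SIB to the bone metastasis might overcome this problem". The Background adds a second aim, "to test shortened fractionation schedules in palliative patients".

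The primary endpoint is bone density in the metastasis, a continuous measure, compared at three months. The Statistical analysis section says that "differences between groups will be calculated using a one-factorial variance analysis". With 30 per group, 80% power and a 5% level, it adds that "it will, however, be possible to detect a standardized mean-value effect (Cohen’s d) of 0.74", on condition that this same one-factorial model is used. The article mentions no SIB contrast, schedule contrast or interaction.

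**The concern.** The layout is a balanced 2 x 2 and each aim corresponds to one factor, yet the named analysis treats the arms as four levels of a single factor. A significant F test shows only that the four means are not all equal. A schedule effect with no SIB effect can produce it, and so can one unusual arm. A non-significant F test does not show that the short schedule is adequate. Either way, answering the two stated aims needs further comparisons that the named analysis does not identify, and these might then be chosen after the results are seen.

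This is not a gap that an unseen analysis plan would simply fill. The article states the model and its number of factors, and ties its detectable effect to that model.

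**Working it through.** **Inputs.** 30 per arm, 120 in total, so 60 with and 60 without SIB, and 60 per schedule (Recruitment and randomization). 80% power, 5% level and d = 0.74 (Statistical analysis). Assumptions: two-sided tests, equal SDs and complete three-month data. Effects are in SD units of the density outcome.

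**1. The plan's own figure.** A two-sided t-test of 30 versus 30 (df 58) has noncentrality d × √(30/2). At d = 0.74 this is 0.74 × 3.873 = 2.87, giving power 80.5%; the detectable d at 80% power is 0.736. So 0.74 is the figure for one uncorrected pair of arms. For the four-arm F test (df 3, 116), power when the largest difference is 0.74 runs from 65% to 93%, depending on the pattern of means.

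**2. Formulas for the two analyses.**
- Omnibus test, df 3, 116: λ = 30 × Σ(mᵢ − m̄)².
- SIB main effect, df 1, 116: λ = 30 × D², where D is the mean of the two SIB arms minus the mean of the two arms without SIB.
- Interaction, df 1, 116: λ = 30 × I²/4, where I is the difference between the two within-schedule SIB effects.

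Power follows from the noncentral F distribution.

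**3. Same SIB effect d in both schedules, no schedule effect.** Arm means are 0, d, 0, d, so Σ(mᵢ − m̄)² = 4 × (d/2)² = d² and both tests have λ = 30d². They differ only in how many degrees of freedom share it.

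| SIB effect (SD) | λ | Omnibus power | SIB main-effect power |
|---|---|---|---|
| 0.4 | 4.8 | 41% | 58% |
| 0.5 | 7.5 | 61% | 78% |
| 0.6 | 10.8 | 78% | 90% |

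For 80% power the omnibus test needs λ = 11.28, so d = √(11.28/30) = 0.61. The main effect needs λ = 7.98, so d = √(7.98/30) = 0.52.

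**4. Attribution.** Apply a 0.5 SD effect to schedule only, with no SIB effect. By symmetry λ is again 7.5, so the omnibus test is significant with probability 61% although SIB does nothing.

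**5. When the advantage disappears.**
- SIB works in one schedule only, by 0.74 SD (means 0, 0, 0, 0.74). Omnibus: λ = 30 × 0.74² × 3/4 = 12.32, power 84%. SIB main effect: D = 0.37, λ = 4.11, power 52%.
- Same pattern at 0.5 SD: 48% omnibus, 27% main effect.
- SIB 0.5 SD plus schedule 0.5 SD, additive: 91% omnibus, 78% SIB main effect. The omnibus figure is higher, but the test still cannot say which factor is responsible.

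**6. Precision** (t with df 116 = 1.98). The 95% CI half-width is 1.98 × √(2/60) = 0.36 SD for a 60-versus-60 main effect, and 1.98 × √(2/30) = 0.51 SD for a within-schedule SIB effect. For the interaction it is 1.98 × √(4/30) = 0.72 SD. Interaction power is 27% for a difference of differences of 0.5 SD and 52% for 0.74 SD; 80% power needs 2 × 0.516 = 1.03 SD.

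**7. Incomplete data.** The article gives no dropout rate. If, as an assumption, 20% to 40% are not evaluable at three months, the detectable SIB main effect rises from 0.52 to between 0.58 and 0.67 SD.

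**The case against.** The strongest defence is that the four-group question is itself stated. Methods/Design announces an evaluation of four schedules in four parallel groups, and the Discussion motivates the trial by the lack of an optimal dose schedule. A one-factorial ANOVA answers whether those schedules differ. A reader might infer that the planned test answers nothing the trial asks; the article does not support that.

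A reader might also infer that the planned test loses power in general. It does not. The gain in step 3 requires similar SIB effects in both schedules and no schedule effect, and step 5 shows the reverse. Unequal effects are plausible, because the factors are not clean: the boost adds 10 Gy over ten fractions in one stratum and over five in the other (1 versus 2 Gy per fraction), and the schedule factor also changes whole-vertebra dose (30 versus 20 Gy). Choosing the pooled SIB effect as the key contrast is therefore a design judgement.

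Setting the factorial contrast against a pairwise comparison corrected for six tests (detectable d 0.91) would also be unfair, because the article adopts no such correction.

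Finally, the study is exploratory, its analyses are described as descriptive, and arm means and SDs will be tabulated. No confirmatory decision depends on the F test, contrasts could be derived from those summaries, and interval reporting may stand in a document not shown.

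All of this limits the severity. It leaves one mismatch: the model named for the primary endpoint does not isolate either of the two stated aims.

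**Conclusion.** The point holds in a limited form. The one-factorial ANOVA addresses whether the four schedules differ at all. It does not attribute a difference to SIB or to schedule, and it leaves the 60-versus-60 comparison unused for both. With equal SIB effects across schedules, no schedule effect, equal SDs and complete data, the cost is 17 percentage points of power at 0.5 SD (78% − 61%) and a detectable effect of 0.61 rather than 0.52 SD. Those figures do not carry over to a SIB effect confined to one schedule. The case for change therefore rests mainly on attribution and estimation, and only conditionally on power. For an exploratory trial this is a change that should be made; it does not invalidate the design.

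**What to change.** In the Statistical analysis section, replace the one-factorial ANOVA with a two-factor model containing SIB (yes/no), schedule (30 Gy in 10 or 20 Gy in 5 fractions) and their interaction.

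- Prespecify the SIB main effect as the key contrast and the schedule main effect as the second, and report both with 95% CIs. Judge the short schedule from its interval, not from non-significance.
- Report the interaction and the SIB effect within each schedule with 95% CIs. State that the interaction is imprecise, that the boost per fraction differs by schedule, and that the schedule factor also changes total dose.
- Restate the detectable effect for the 60-versus-60 contrast (0.52 SD at 80% power with complete data), and label 0.74 as the figure for one pair of arms if it is kept.
- Keep all results labelled exploratory.

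The cost is analysis wording only, with no change to patients, arms or measurements. It should be settled before outcome data are seen. The downside is that the pooled SIB effect averages over two different boost schedules, which is why the within-schedule effects must appear beside it.

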## Background

Two-thirds of all cancer patients develop bone metastases during the course of their disease [1]. This form of distant relapse occurs from many types of solid cancers, especially from lung, breast, and prostate [2]. Bone involvement can also be extensive in certain hematologic malignancies [3, 4]. About 30% of all skeletal metastases and 10% of all primary bone tumors are located in the spinal column [5], mostly the lumbar (52%), thoracic (36%), and cervical (12%) spine [6]. The exact mechanism of bone metastasis is not fully understood. It is postulated that bone metastases arise as a detachment of tumor cells from the primary tumor and reach the bone by intravascular penetration, resulting in adhesion in distinct bone areas. The tumor cells cause local changes of the bone structure, caused by an imbalance of bone remodeling. Bone metastases present as osteoplastic, osteolytic, or mixed osteolytic/osteoplastic tumor masses. Many metastatic bone lesions cause few or no symptoms, but for skeletal-related events, pain is the most common symptom; many patients with bone metastasis experience significant pain at some point during their disease course [7]. Other skeletal-related events include reduce activity in daily life (ADL), decreased energy, hypercalcemia, and risk of pathological fractures and neurological deficits. Pathologic bone fractures occur in 5% and spinal cord compression in 10–15% [5]. Restrictions of movement of the spinal column may have a devastating long-term impact on function, mobility, independence, health, and quality of life (QoL). External beam radiotherapy has an established role in the management of patients with bone metastases of the spine. The fractionation schedule applying 30 Gray in ten fractions is a safe and effective treatment modality commonly used to achieve palliation of pain associated with spinal metastases [8]. In about 50–80% of the patients, a decrease of pain is reported and about 30% of the patients showed complete remission of pain [8]. Stereotactic body radiation therapy (SBRT) using intensity-modulated radiotherapy (IMRT) can be a safe treatment option for treating spinal metastasis with enhanced targeting accuracy [9, 10]. Published data report that IMRT to the spine was well tolerated, had no significant late toxicities, and spared other organs at risk [11]. Pre-treatment megavoltage computed tomography (CT) allows for the control of the patient position and improves treatment accuracy [12].

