### Assessment of the primary and secondary endpoints

The aim of the study is to evaluate local control rates in metastatic bone disease. The primary endpoint is defined by bone remodeling according to density in the metastasis. Bone density will be measured at the irradiated region at baseline and at the three-month time-point after the completion of RT (t_2_). Furthermore, the local control is assessed by CT imaging taken before and at three and six months after radiation treatment. Secondary endpoints are vertebral stability, QoL, fatigue, pain, overall survival, bone survival, pathological fracture, and neurological deficits. The baseline examination will be carried out immediately before the start of therapy and is scheduled to comprise the comprehensive recording of the socio-demographic data, the recording of the current pain situation (VAS score), the extent of fractures, the QoL, and the current degree of fatigue. The follow-up examinations will take place after the end of RT, as mentioned above (Fig. 1).

The secondary endpoints such as overall survival, fatigue, QoL, and anxiety will be recorded by using validated questionnaires (EORTC QLQ FA13 [14], EORTC QLQ BM22 [15], and the questionnaire to record stress in patients with cancer [FBK] according to Book et al. [16]). All patients will also be asked to record their pain history by using a pain diary (documentation of medication daily during treatment and once weekly after the completion of treatment, VAS pain scale). The pain response is documented on the VAS (range of 0–10). Complete response is defined as VAS score of 0/10 after three or six months and partial response is defined as a reduced value by at least 2 points after three or six months, according to the international consensus response categories by Chow et al. [17]. Overall survival is defined as time from initial diagnosis until death and bone survival is defined as time from initial diagnosis of irradiated spinal bone metastasis until death (Additional file 1).

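### Pain response is graded in ordered steps, but the one test named for categorical variables ignores the order and gives up about 9 to 13 points of power against a shift

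*Protocol article*

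**What the plan says.** All references are to the protocol article.

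- **Assessment of the primary and secondary endpoints.** Pain is one of eight secondary endpoints: "Secondary endpoints are vertebral stability, QoL, fatigue, pain, overall survival, bone survival, pathological fracture, and neurological deficits". Two grades of response are defined on the 0–10 VAS. The upper grade, complete response, needs a score of zero at follow-up. The lower grade reads: "partial response is defined as a reduced value by at least 2 points after three or six months". No response is not written out, but it is what remains.
- **Statistical analysis.** One sentence covers every categorical variable: "Differences of categorical variables will be calculated with the Chi-square test". It names no variable and makes no exception for ordered categories. The same section describes the study as explorative and adds: "All statistical analyses will be carried out descriptively using SAS software Version 9.4 or higher".
- **Background.** For 30 Gy in ten fractions, pain decreases in 50–80% of patients, and "about 30% of the patients showed complete remission of pain".

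**The concern.** Complete, partial and no response run from best to worst. On a table of four arms by three levels, Pearson's Chi-square test has (4 − 1) × (3 − 1) = 6 degrees of freedom, and its p-value is the same if the three levels are relabelled in any order. A consistent move towards better response therefore gets no more weight than any other departure. A test on mean ranks has 3 degrees of freedom and is aimed at such a move.

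The Discussion reasons in one direction: dose escalation is expected to improve tumour control, and pain reduction is listed among the goals of therapy. A shift is thus the natural pattern to look for. With 30 patients per arm, and a sample size not derived from pain response, a real shift would be missed more often than necessary.

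**Working it through.** **The plan's own figure.** The only power statement is d = 0.74 with 30 per group, 80% power and 5% significance. As a two-sided two-group t-test, the noncentrality is 0.74 × √(30/2) = 2.866 on 58 degrees of freedom, which gives power 0.805. The figure reproduces in that form. It concerns a mean and says nothing about pain response, so the rest of this check leaves it untouched.

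**Inputs**
- From the article: four arms of 30; 5% level; complete response about 30%; any decrease 50–80%.
- Derived: partial response 20–50% and none 50–20%. Three base splits (complete/partial/none) span this: 30/35/35, 30/20/50 and 30/50/20.
- Assumed: both SIB arms are shifted by a common odds ratio (OR) of 2, 2.5 or 3; the two arms without SIB stay at base; all 120 patients are evaluable; the reported decrease of pain corresponds to the 2-point definition and includes the complete responders.

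**One case by hand: base 30/35/35, OR 3**
1. Shift the cumulative odds. 0.30/0.70 × 3 = 1.286, giving 0.5625. 0.65/0.35 × 3 = 5.571, giving 0.8478. The SIB arms become 56.25/28.53/15.22%.
2. Chi-square noncentrality. With two arms at base and two shifted, it is 30 × Σ dⱼ²/p̄ⱼ, where dⱼ is the difference and p̄ⱼ the average of the two splits. Here that is 30 × (0.2625²/0.4313 + 0.0647²/0.3177 + 0.1978²/0.2511) = 30 × 0.3288 = 9.86.
3. Kruskal-Wallis noncentrality. The expected level totals are 51.75, 38.12 and 30.13, with mid-ranks 26.4, 71.3 and 105.4 and overall mean rank 60.5. The arm mean ranks lie 9.27 above or below 60.5. The tie-corrected rank variance is (51.75 × 34.1² + 38.12 × 10.8² + 30.13 × 44.9²)/119 ≈ 1,055. H = 120 × 9.27²/1,055 ≈ 9.78.
4. Power. P(χ²₆ with noncentrality 9.86 > 12.59) = 0.64. P(χ²₃ with noncentrality 9.78 > 7.81) = 0.75.

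The signal is almost the same (9.86 and 9.78). The Chi-square test spreads it over twice the degrees of freedom.

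**Noncentral chi-square approximation, all cases (Chi-square / Kruskal-Wallis)**

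| Base split | OR 2 | OR 2.5 | OR 3 |
|---|---|---|---|
| 30/35/35 | 28% / 37% | 47% / 59% | 64% / 75% |
| 30/20/50 | 27% / 36% | 47% / 58% | 63% / 75% |
| 30/50/20 | 27% / 35% | 45% / 57% | 61% / 73% |

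**Simulation, 20,000 trials per case, over the same three splits**

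| | OR 2 | OR 2.5 | OR 3 |
|---|---|---|---|
| Chi-square, 6 df | 26–28% | 44–47% | 62–65% |
| Kruskal-Wallis, 3 df | 35–37% | 57–59% | 74–77% |

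The gap is about 9–13 points. With no effect, both tests reject in about 5% of trials.

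**Other patterns**
- Only one of the four arms shifted: 20–21% against 26–28% at OR 2, and 48–50% against 60–63% at OR 3.
- A crossing pattern (base 30/35/35; SIB arms 45/5/50 or 50/10/40, so complete and none both rise): Chi-square 93% and 73%, Kruskal-Wallis 5% and 11%. The ranking reverses.

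**The case against.** **Nothing stated is false.** The Chi-square test holds its level, the article claims no power for pain response, and the analyses are called descriptive. This stands, and it limits the point to efficiency.

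**The analysis plan may settle it.** The sentence is a general default in a condensed article, and the test for each endpoint is often fixed elsewhere. This stands in part: the article does name a test for all categorical variables, and read as written it covers graded pain response.

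**The three-level variable is inferred.** Only two grades are defined, and the cited consensus categories are not in the article. A yes/no responder analysis, or the VAS score itself, would also fit the text. This stands, so the fix is conditional on a graded comparison. Dichotomising does not recover the loss, however. For base 30/35/35 at OR 2, 2.5 and 3, the Chi-square test on any response has 26%, 41% and 54% power, and on complete response 30%, 51% and 69%. The Kruskal-Wallis test has about 36%, 59% and 76%.

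**The gain depends on the pattern.** This stands. No treatment effect on pain is given in the article, and a crossing pattern favours the Chi-square test heavily. The dose-escalation rationale makes a shift more plausible but does not establish it.

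**Conclusion.** The point holds as a minor matter of efficiency. If pain response is compared as complete, partial or none, the named test gives up about 9–13 points of power against a common shift in both SIB arms. That result rests on an assumed odds ratio of 2 to 3, proportional odds, full evaluability, and base rates read from the Background. The primary endpoint and the stated d = 0.74 are unaffected.

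A reader might infer more than the article supports:
- **That the Chi-square test is wrong here.** It is valid; only its sensitivity to a shift is at issue.
- **That adverse event grades have the same problem.** The Abstract lists adverse events as secondary endpoints, but the article gives no grading scale, so there is no stated ordered variable to criticise.
- **That pain is the leading secondary endpoint.** It stands fourth of eight, with no ranking given.
- **That the loss can be sized by pooling both SIB arms against both arms without SIB.** The Statistical analysis section plans no such pooled comparison.

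**What to change.** Add to the Statistical analysis section, or to the analysis plan, wording such as: *Pain response (complete, partial, none), if compared as graded categories, is compared across the four arms by the Kruskal-Wallis (row mean score) test with correction for ties. Odds ratios with 95% confidence intervals from a proportional-odds model are given for each SIB arm against the same schedule without SIB. The number and percentage in each category are shown by arm. The Chi-square test is used for unordered categorical variables.*

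Naming the two contrasts matters, because a single common odds ratio is undefined among four arms. Each contrast compares 30 with 30 patients, where the rank test has only about 30% power at OR 2 and 61% at OR 3 (base 30/35/35). The odds ratios are therefore estimates with wide intervals.

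The cost is a few sentences and no extra data. The price is little power for patterns that are not a shift, which is why the full table stays, and a proportional-odds assumption that should be checked against that table. The article reports recruitment as not completed, so the wording could be set before outcomes are analysed.

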### Inclusion criteria

Patients with histologic confirmation of a tumor disease, demonstrating metachronic solitary or multiple metastatic bone lesions of the thoracic or lumbar spine or the sacral boneIndication for RT of the bone metastasesMRI-based staging examinations (if necessary)Age 18–85 yearsKarnofsky Index ≥ 50% [13]Signed declaration of informed consent

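### Survival is compared only by an unadjusted log-rank test across mixed primary tumours. The test is valid, but a Cox model adjusted for primary tumour and Karnofsky Index would be a low-cost improvement.

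*Protocol article*

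**What the plan says.** The article's Statistical analysis section gives survival one sentence: "The survival analysis will be performed using the Kaplan–Meier method and log-rank test". It names no stratum, covariate or regression model, and calls all analyses descriptive.

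Under Assessment of the primary and secondary endpoints, survival is secondary: "Secondary endpoints are vertebral stability, QoL, fatigue, pain, overall survival, bone survival, pathological fracture, and neurological deficits". The clock for overall survival starts before randomization: "Overall survival is defined as time from initial diagnosis until death".

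The population is mixed. The first inclusion criterion opens with "Patients with histologic confirmation of a tumor disease" and does not restrict the primary site. Karnofsky Index of at least 50% is also required. Myeloma, lymphoma and sarcoma are excluded. The Background says of bone metastasis: "This form of distant relapse occurs from many types of solid cancers, especially from lung, breast, and prostate".

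Allocation is described under Recruitment and randomization: "A block randomization procedure will be used to ensure even distribution of patients into the four groups". The size is "120 patients in total, 30 patients in each group". No prognostic factor is named for the blocks.

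**The concern.** Patients with different primary tumours and different performance status may have very different survival. As described, neither the randomization nor the analysis uses these two baseline facts, although eligibility requires histology and Karnofsky Index for every patient.

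Two things follow with 30 patients per arm. The arms can differ by chance in their prognostic mix, which makes the observed survival contrast harder to read. And even with balanced arms, leaving out a strong prognostic factor weakens the comparison. At stake is the precision and readability of two secondary endpoints. The bone-density primary endpoint is not involved.

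**Working it through.** **Inputs from the article.** Four arms of 30, 5% significance level, follow-up to two years after enrolment, log-rank test without strata.

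**The plan's own figure.** No event count, hazard ratio or power is given for survival. The only power statement concerns the primary endpoint, a Cohen's d of 0.74 "with a power of 80% and a significance level of 5"%. It reproduces as a two-sided t-test of two groups of 30 (power 80.5%, detectable d 0.736), which supports reading the 5% as two-sided. It says nothing about survival.

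**Assumptions, not in the article.**
- Exponential survival timed from randomization, with a median of about 14 months and censoring at 24 months.
- Four tumour groups in proportions 30/25/20/25%, and 40% of patients with low Karnofsky Index.
- Hazard for patient i: (ln 2 / 14) × exp(p_i − mean(p) + treatment effect), where p_i = log(tumour HR) + log(Karnofsky HR).
- Prognostic strength (tumour HRs; low-Karnofsky HR): none; weak (1, 1, 1.5, 1.5; 1.5); strong (1, 1, 2, 3; 2); very strong (1, 1.2, 3, 5; 2.5).

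**Tests.** (a) Plain log-rank. (b) Log-rank stratified by tumour × Karnofsky: with d = Σ(O − E) and V = ΣVar summed over strata, χ² = d′V⁻¹d. (c) Wald test from a Cox model with tumour group and Karnofsky Index as covariates. There were 1,500 trials per cell, with a Monte Carlo error of about 1.3 points on power.

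**Power, boost vs no boost (60 vs 60), HR 0.6**

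| Prognosis | Plain | Stratified | Adjusted Cox | Cox − plain |
|---|---|---|---|---|
| None | 60.3% | 56.3% | 59.6% | −0.7 |
| Weak | 56.6% | 53.6% | 56.5% | −0.1 |
| Strong | 48.3% | 54.1% | 57.7% | +9.5 |
| Very strong | 39.3% | 52.1% | 55.0% | +15.7 |

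**Power, four-arm test, one arm at HR 0.45**

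| Prognosis | Plain | Stratified | Adjusted Cox | Cox − plain |
|---|---|---|---|---|
| None | 60.9% | 55.7% | 58.5% | −2.5 |
| Weak | 58.7% | 57.0% | 59.3% | +0.6 |
| Strong | 49.0% | 53.1% | 57.7% | +8.7 |
| Very strong | 41.6% | 55.3% | 60.3% | +18.7 |

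In the strong and very strong rows the plain test falls short by 4.1 points (53.1 − 49.0, stratified, four-arm) to 18.7 points (60.3 − 41.6, Cox, four-arm). With no prognostic effect, fine stratification costs up to 5.3 points (60.9 − 55.7, before rounding) and the Cox model up to 2.5.

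**Type I error.** Plain 3.6–5.7%, stratified 4.3–6.0%, Cox Wald 4.5–7.1%. The Monte Carlo error here is √(0.05 × 0.95 / 1500) = 0.56 points. The highest Cox value is in the four-arm test.

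**A second, simpler model.** Three equally common tumour groups, HR 0.6 in both boost arms, four-arm log-rank, plain vs stratified by tumour group:
- medians 8/12/16 months: 43% vs 46%
- medians 5/12/20 months: 35% vs 46%
- medians 4/12/30 months: 28% vs 44%

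For the same three sets of medians at HR 0.8, power is 13/10/9% plain and 13/11/10% stratified. At HR 0.9 both are 6–7%.

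**Chance imbalance.** Assume 45% of patients have a poor prognosis. For 30 vs 30 the SD of the difference in shares is √(2 × 0.45 × 0.55 / 30) = 0.128, so a gap of 10 points or more has probability 44%, and of 20 points or more 12%. For 60 vs 60 the SD is 0.091, and a gap of 10 points or more has probability 27%.

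**The case against.** The strongest case against is that nothing here is wrong. A log-rank test needs no strata to be valid under randomization, and its error rate already includes chance imbalance. **This stands.** A reader might infer that imbalance biases the survival result. The simulated size near 5% shows otherwise.

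Second, the power loss rests on prognostic strengths and boost effects that the article does not give. **This also stands.** One might infer that tumour type and performance status outweigh any boost effect on survival, but the article gives no figure for either. With weak prognosis there is no material loss, and at HR 0.8 or 0.9 the gain is about one point or none.

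Third, the imbalance can be made to look worse than it is. For a tumour type in one third of patients, a gap of 20 points or more somewhere among the four arms has probability 43%, but that takes the largest of six pairs. For one given pair it is 13%, and for 60 vs 60 it is 2.6%.

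Fourth, a supportive model or stratified blocks may be described in the full protocol or the analysis plan, neither of which is shown. **This stands in part.** Silence about strata does not prove that there are none. But the article does name its survival test, and that stated choice can be improved.

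Fifth, the unadjusted hazard ratio of 0.61 to 0.68 under the second model, against a true 0.6 within tumour groups, might be read as an error. It is not. It is a marginal instead of a conditional quantity, and the plan promises no hazard ratio.

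**Conclusion.** The point holds as a minor improvement to a secondary, exploratory analysis. The planned test is valid. It gives up about 4 to 19 points of power if primary tumour and Karnofsky Index are strongly prognostic and the treatment effect is large (boost HR 0.6, or one arm at 0.45). It gives up little or nothing otherwise. An adjusted Cox model has the better balance of risk: it gained 9 to 19 points in the strong and very strong scenarios and lost at most 2.5 points when there was nothing to adjust for. Part of its four-arm gain reflects a slightly raised type I error.

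All these figures assume survival timed from randomization. The article times overall survival from initial diagnosis, which a standard log-rank test does not handle without allowing for delayed entry. That is a separate and larger problem, and covariate adjustment does not cure it.

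**What to change.** Keep the Kaplan–Meier curves and the log-rank test. Add a pre-specified Cox model with treatment, a few broad primary-tumour groups (for example breast, prostate, lung, other) and Karnofsky Index. Fix the grouping and the form of Karnofsky Index before any outcome data are seen. Report the adjusted hazard ratio with its confidence interval as the main survival estimate.

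Do not cross-stratify tumour by Karnofsky Index. Four tumour groups by two Karnofsky levels make 8 strata, and 120 / (8 × 4) is fewer than 4 patients per arm and stratum.

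**Cost.** Analysis wording only, since eligibility already requires both facts. The downsides are:
- four extra parameters in a small trial (three for tumour group, one for Karnofsky Index);
- a conditional instead of a marginal hazard ratio, which should be labelled as such;
- a slightly raised Wald type I error in the four-arm test, up to about 7%. A repeat of the same model with Wald, likelihood-ratio and score tests showed similar sizes for all three, so changing among them should not be relied on to remove it. Keeping the log-rank p-value alongside is the simple safeguard, and a re-randomization test is available if exact size is wanted.

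The time origin of overall survival needs its own correction.
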